### Heterogeneity tests

Populations from diverse genetic, socio-cultural and socio-economic backgrounds can be quite different in their characteristics. Additionally, there may be some disparities between sites with respect to the quality and quantity of data items that each site can measure. This is expected regarding a data collection that allows any site to contribute. Consequently, heterogeneity in effect estimates may be due to clinical differences between pregnant women and/or site-level differences in terms of exposure and outcome determination (reporting or assessment bias). We will formally assess heterogeneity taking into account variations in exposure, covariates, and significant outcomes, and use meta-analysis methods (Q or I statistics, meta-regression, and subgroup analysis) to unravel heterogeneity at central and individual levels. Briefly, we will incorporate individual-level interaction terms in one-stage analysis and random intercepts to account for central-level factors not measured in the regression models mentioned above.

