### Patients

Case eligibility criteria included individuals with laboratory confirmation of COVID-19 infection, irrespective of clinical signs and symptoms or the result of another serological test. Positive RNA PCR test from maternal nasopharyngeal swabs.

The selection of the control group will be collected in the same database, considering patients with negative COVID-19 delivery diagnosed by PCR screening at the time of delivery or less than 3 days before.

The delivery or deliveries that were treated in this site and that occurred within the same day, before and after the case (maximum 3 per case), are included in the control group. If the case were the last delivery of the day, the first ones of the following day could be recruited. If the case were the first of that day, the last one of the previous day could be recruited.

The data collected will be entered at the time they join the registry.

Delivery monitoring: the *outcomes* include perinatal and neonatal events, which were collected at the time of delivery and the days immediately afterward. These perinatal events included gestational age, type of delivery, presence of prepartum or premature rupture of membranes before delivery, as well as any medical complications (thromboembolic events, admission to ICU, maternal death) and obstetric complications (hemorrhagic events and hypertensive disorders), while neonatal events included the 5-minute Apgar score, the pH of the umbilical artery and possible complications such as admission to the NICU and neonatal death in the follow-up period or intrauterine foetal death. The definitions of obstetric pathology follow the international criteria of the ACOG and RCOG (18-21).

Follow-up after delivery: Patient follow-up is carried out by the local investigator over the phone and the medical history is consulted from the time the patient is discharged up to 6 weeks later in order to detect late postpartum complications related to COVID 19. In the case of the new-born, the follow-up is 14 days by the investigating neonatology department by telephone and consultation of the patient's medical history to detect symptoms of COVID 19 symptoms. Complications recorded in the mother during this period (mastitis, endometritis, pulmonary embolism) as well as neonatal death or readmission of the new-born due to COVID were considered *outcomes* of interest and analysed together with those described above.

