### Statistics

For the descriptive analysis, categorical variables were expressed as absolute and relative frequencies; whereas quantitative ones were expressed as mean and range (minimum-maximum values). Analysis of the possible association of both the characteristics of the patients and the *outcomes* collected with COVID-19 infection is carried out using the Pearson Chi-square test or Fisher's exact test and the Mann-Whitney U test (after checking the absence of normal data using the Kolmogorov-Smirnov test). See sections of Data Quality Plan and sample size. Statistical significance was established with  $P < 0.05$ . All statistical analyses were carried out with SAS 9.4 software.

For each response variable (*outcome*) a multiple logistic regression model has been carried out, refined with the backward conditional stepwise method.

The response variables are those described in the previous section. The subset of explanatory variables is different for each model and is specified in the text.

It will only be of interest the Odds Ratio (OR), its 95% CI and the significance of the “COVID” factor. The information on the rest of the explanatory variables is irrelevant since they only act as adjustment variables.

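### Substudy 3 picks controls by site and delivery day with a variable ratio, but its named analysis has no matching term, so the COVID odds ratio can be biased if outcome risk varies with the ratio

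*Protocol*

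**What the plan says.** **Control selection (Protocol, Substudy 3, Patients).** Controls are PCR-negative deliveries from the case's site that "occurred within the same day, before and after the case (maximum 3 per case), are included in the control group". Moving to a neighbouring day is allowed at the edges of the day: "If the case were the last delivery of the day, the first ones of the following day could be recruited", and likewise backwards when the case is the first delivery. The word matching is not used, and no minimum or fixed number of controls is set.

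**Analysis (Substudy 3, Statistics).** Associations with infection are tested with the "Pearson Chi-square test or Fisher's exact test and the Mann-Whitney U test". For each outcome, "a multiple logistic regression model has been carried out, refined with the backward conditional stepwise method". On covariates: "The subset of explanatory variables is different for each model and is specified in the text", but no list follows. The section then narrows the reported result: "It will only be of interest the Odds Ratio (OR), its 95% CI and the significance of the" COVID factor. Its only cross-references are to the data quality and sample size sections.

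**Centre effects (Heterogeneity tests).** This registry-wide section plans a one-stage analysis with "random intercepts to account for central-level factors not measured in the regression models mentioned above". No regression model precedes it in the protocol.

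**The concern.** Taking controls from the same hospital on nearly the same day balances local practice and the phase of the epidemic between infected and uninfected women. That balance carries through to a pooled analysis only if every case brings the same number of controls. If small units supply one control per case and large units three, the pooled control group leans towards large units while the cases do not. Any difference in outcome risk between the two kinds of unit then enters the COVID odds ratio.

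The methods named for Substudy 3 do not guard against this. The chi-square, Fisher and Mann-Whitney tests treat the groups as independent samples. The term conditional in the description of the stepwise method names a rule for removing variables; it does not mean conditional logistic regression. Since the COVID odds ratio is the only result of interest, any bias falls on the headline estimate.

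**Working it through.** Substudy 3 gives no sample size, event rate or expected odds ratio, so there is no figure to reproduce. The question is whether the ratio could vary, and what follows if it does.

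**1. Could the ratio vary?** The section on overall sample size gives 172,000 deliveries in 100 sites: 172,000 / 100 / 365 = 4.7 deliveries per site per day on average. Assume the number of other deliveries on the day is Poisson with mean (annual volume / 365). The chance of fewer than 3 is then:
- 400 deliveries a year: 90%
- 800 a year: 62%
- 1,720 a year (the average site): 15%
- 3,000 a year: 1%

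This is before the limited use of neighbouring days, which raises availability, and before the PCR-negative requirement, which lowers it. The volumes other than 1,720 are illustrative.

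**2. Pooled odds ratio when the true value is 1.** Take small and large units (k) with share of cases s_k, outcome risk p_k and r_k controls per case. All are assumptions.
- Case risk = Σ s_k p_k
- Control risk = Σ s_k r_k p_k / Σ s_k r_k
- Pooled OR = ratio of the two odds

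Worked once, with half the cases in each type, risks 6% and 12%, and 1 and 3 controls per case: case risk = 0.5 × 6% + 0.5 × 12% = 9.0%. Control risk = (0.5 × 1 × 6% + 0.5 × 3 × 12%) / (0.5 × 1 + 0.5 × 3) = 21% / 2 = 10.5%. OR = (0.090/0.910) / (0.105/0.895) = 0.84.

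| Case share, small/large | Risk, small/large | Controls per case, small/large | Case risk | Control risk | Pooled OR |
|---|---|---|---|---|---|
| 50/50 | 6%/12% | 3/3 | 9.0% | 9.0% | 1.00 |
| 50/50 | 6%/12% | 2/3 | 9.0% | 9.6% | 0.93 |
| 50/50 | 6%/12% | 1/3 | 9.0% | 10.5% | 0.84 |
| 50/50 | 6%/10% | 1/3 | 8.0% | 9.0% | 0.88 |
| 20/80 | 6%/12% | 1/3 | 10.8% | 11.5% | 0.93 |
| 10/90 | 6%/12% | 1/3 | 11.4% | 11.8% | 0.96 |
| 50/50 | 6%/12% | 3/1 | 9.0% | 7.5% | 1.22 |

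The last row equals the case where small units have the higher risk and the fewer controls. With equal risks the pooled OR is 1.00 at any ratio.

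**3. False-positive rate.** The unmatched two-proportion test was simulated with 1,000 cases, half in each type of unit, at a nominal 5% (risk pairs 8%/12%, 5%/10% and 5%/15%). It rejected in about 5% of runs at a constant 3 controls, 7–15% at 3 and 2, and 14–63% at 3 and 1.

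**4. Constant ratio with a real effect.** At 3 controls throughout and a true OR of 1.5, the pooled OR in the same scenarios was 1.48–1.50. This is slight attenuation, not confounding.

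**5. Does a site random intercept cure it?** Simulation of 100 sites with 10 cases each, 1 to 3 controls per case by site size, true OR 1:
- Risk rising with size: pooled 0.88, random intercept 0.92, site-stratified 1.00.
- Risk falling with size: pooled 1.15, random intercept 1.10, site-stratified 1.00.

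The random intercept leaves more than half the bias. It assumes that site effects are unrelated to the share of a site's women who are cases, and that assumption fails here.

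**The case against.** Four points can be made for the plan.

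- **Site may be among the covariates.** They are said to be specified elsewhere, and such lists are often left to an analysis plan. A reader might infer that the plan definitely discards the matching. The text does not go that far: it is silent on site and date. What stands is that it fixes the tests and the model type, names no matching term, and lets backward selection remove terms.
- **Centre effects are mentioned.** The random intercepts may be meant for the substudy regressions, which come later in the document, so calling the model plain logistic regression without qualification would be too strong. The link is not made, however, and date, matched set and univariable tests stay uncovered. Step 5 shows that the device is only a partial remedy.
- **A variable ratio alone is harmless.** This is correct. Controls are chosen by exposure status, so this is a matched cohort. Bias also needs baseline risk to differ in line with the ratio. The plan makes differences in risk plausible by expecting populations and outcome ascertainment to differ between sites, but does not show that they follow the ratio.
- **Small units may contribute few cases.** Also fair: at a 20% share the 0.84 becomes 0.93, and at 10% it becomes 0.96.

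A reader might also infer that clustering within sites makes the standard errors wrong. That has not been shown. With a constant ratio, the simulated false-positive rate stayed near 5%.

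**Conclusion.** The analysis named for Substudy 3 does not fit its control selection, and the safeguard for centre effects is neither linked to it nor sufficient. The resulting bias is conditional: it needs both a control ratio that varies between sites and a baseline risk that varies with that ratio. Under the assumed 6% and 12% risks and 1 and 3 controls per case, a true odds ratio of 1 appears as anything from 0.84 to 0.96, depending on the share of cases in small units, or as 1.22 with the ratios reversed and half the cases in each type. The documents give no site-specific risks, ratios or case shares, so neither the direction nor the size can be fixed from them. If nearly every case has three controls, little changes. The point still merits correction, because it touches the one estimate the substudy reports and the remedy is cheap.

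**What to change.** In Substudy 3, Statistics:

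1. Take the primary COVID odds ratio from conditional logistic regression stratified on the matched set (the case and its controls). For sparse outcomes, use a logistic model stratified on site, or with site as a fixed effect, plus calendar time. Do not rely on a site random intercept alone.
2. Force the matching terms into the model, outside backward selection.
3. Use Mantel-Haenszel or other stratified tests for the unadjusted comparisons.
4. Keep an identifier linking each control to its case. The variable list is a separate file not seen here, so one may already exist; if not, site and delivery date allow the stratified version.
5. State how cases with fewer than three controls, or none, are handled, and report the distribution of controls per case by site.
6. Reconcile the Heterogeneity tests section with this model.

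**Cost.** At most one identifier, and a STRATA statement in the SAS logistic procedure. The real price is information: sets without controls or without variation in the outcome do not contribute to the conditional analysis. This matters most for rare outcomes, which is why the site-stratified alternative should be specified in advance.

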## Study population and selection criteria

For the characterization of the clinical course of SARS-CoV-2 infection during pregnancy, the pre-study sample size calculation has not been carried out, as registry-based studies generally tend to be comprehensive without involving hypotheses.

Patients eligible for follow-up of target population will be any pregnant woman who is suspected or needs to be ruled out as having a SARS-CoV-2 infection at any time during pregnancy with positive test results for SARS-CoV-2 by PCR.

Information regarding each pregnant woman's demographic characteristics, comorbidities and current obstetric history was extracted from the medical history and the patient interview; subsequently, age and race were categorized according to the classification used by the Center for Disease Control and Prevention (CDC) (17).

For the selection of the control group to be collected in the same database, patients with a negative COVID-19 delivery diagnosed by PCR screening at delivery, or less than 3 days before, were considered.

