### Exclusion criteria

Pregnant women under the following conditions will be excluded from the registry:

- Inability to give informed consent in the absence of a legal representative.
- If, in the opinion of the researcher, findings in the physical examination, anomalies in the results of the laboratory tests or other medical, social or psychosocial factors could have a negative influence.
- Loss of follow-up data prior to 6 weeks postpartum.

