## Data sources and work plan

### Patient referral sources

If the doctor in charge considers it appropriate to inform the patient about the existence and purpose of this registry, he/she may do so. At this time, consent will be requested so that the information derived from the regular monitoring of these patients is incorporated into the data registry, and that said information can be analysed and disclosed for scientific purposes in accord with the confidentiality provisions of the current legislation.

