## Informed consent

In accordance with the criteria of good clinical practice, the subjects will be duly informed of all those details concerning their participation in the study and will freely give their consent in writing or orally, recording this fact in their medical records.

Preferably written or oral consent will be sought for cases and controls chosen at random from among pregnant women who have given birth in each centre and who have COVID-19. The patient may sign the consent electronically (See appendix 7).

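### Substudy 3's control rule fixes site, day and a cap of three but no order, so controls could be chosen with delivery outcomes visible; the consent section describes different controls

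*Protocol*

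**What the plan says.** The working rule is in the Protocol, Substudy 3, Patients. Deliveries at the same site "within the same day, before and after the case (maximum 3 per case), are included in the control group". Two fallbacks cover the edges of the day. If the case is the last delivery, "the first ones of the following day could be recruited"; if she is the first, "the last one of the previous day could be recruited".

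Eligibility is in Study population and selection criteria: for the control group, "patients with a negative COVID-19 delivery diagnosed by PCR screening at delivery, or less than 3 days before, were considered". Substudy 3 repeats this, so in both places the comparator is PCR-negative.

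The Informed consent section describes the participants to be asked as "cases and controls chosen at random from among pregnant women who have given birth in each centre and who have COVID-19".

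Substudy 3, Statistics, makes the odds ratio for the COVID factor the only estimate of interest, so the choice of comparator bears directly on the result.

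**The concern.** Two sites could follow the rule faithfully and enrol different controls for the same case. The text does not say which women are taken when more than three qualify, how many come from before and how many from after the case, whether the nearest come first, or who replaces a woman who is ineligible or declines. It sets a ceiling without a minimum. The fallbacks permit recruitment without requiring it, and one of them gives no number.

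A control is identified by when she delivered relative to the case, so she is identified only once she has delivered. Type of delivery, gestational age, Apgar score and cord pH can then be known, and sometimes haemorrhage or NICU admission. If convenience favours uncomplicated women, the event rate among controls falls and the odds ratio rises. Covariate adjustment cannot undo selection on the outcome itself.

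The consent section adds a second description that conflicts on both mechanism and infection status. Sites and ethics committees read that section.

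**Working it through.** Substudy 3 states no sample size, power or effect, so there is no figure of the plan to reproduce. The check has three parts.

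**1. Two descriptions of the controls**

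| | Substudy 3, Patients | Informed consent |
|---|---|---|
| Mechanism | Deliveries around the case, same site and day, at most 3 | Random choice |
| Infection status | PCR-negative | Women with COVID-19 |

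They cannot both hold on either row.

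**2. How often the cap leaves a choice**

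Inputs from Overall sample size: 172,000 deliveries in 2019 at 100 sites.

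172,000 / 100 / 365 = 4.71 deliveries per site per day.

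Assume that the number K of other same-day deliveries is Poisson with this mean (the documents give no distribution), and vary the volume:

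- half the average (2.36): P(K > 3) = 21%
- average (4.71): P(K > 3) = 69%
- twice the average (9.42): P(K > 3) = 98%

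These counts include women who are PCR-positive or decline, so the eligible pool is somewhat smaller. They also count every same-day woman. If the before-and-after wording means adjacent deliveries, the choice narrows, but one before and two after, two before and one after, or three after all still comply.

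**3. What selection could do (illustration only)**

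Let complicated women be enrolled r times as often as uncomplicated women, with r_case among cases and r_control among controls. With a true odds ratio of 1, the observed odds in each group are the true odds multiplied by that group's r, so

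observed OR = r_case / r_control.

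- r_case = 1, r_control = 0.80: 1 / 0.80 = 1.25
- r_case = 0.80, r_control = 0.80: 1.00
- r_case = 0.67, r_control = 0.80: 0.67 / 0.80 = 0.84

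A simulation with a different mechanism gives values of the same order. It used 200,000 cases per setting, a true OR of 1, and outcome risks of 5%, 10% and 25%. For a share f of cases the site fills the three places with event-free women first; otherwise it chooses at random. Case enrolment is unrelated to outcome.

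| Volume | f = 10% | f = 25% | f = 50% |
|---|---|---|---|
| Half | 1.03–1.04 | 1.08 | 1.17–1.18 |
| Average | 1.07–1.09 | 1.23–1.24 | 1.59–1.61 |
| Twice | 1.12–1.14 | 1.34–1.42 | 2.03–2.24 |

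The simulation treats any same-day woman as a candidate, so it reflects the loosest reading of the rule. Neither r nor f comes from the documents. With a fixed order f = 0, and this route of bias closes.

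**The case against.** The strongest reply is that the rule is far from a free pick. It fixes site, day and position around the case, and the fallbacks make sense only if adjacency is intended. That stands: the gap lies in the order, the number, replacement and the permissive fallbacks.

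The direction of bias is also open. Discretion over entry covers the whole registry: "If the doctor in charge considers it appropriate to inform the patient about the existence and purpose of this registry, he/she may do so". Exclusion is likewise allowed where, in the researcher's opinion, "other medical, social or psychosocial factors could have a negative influence". If complicated cases are under-enrolled too, the ratio can be 1 or below. Women with complications may also stay longer and be easier to approach. This stands, and it is why 1.25 is only an illustration.

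Data collection places inclusion at the time of the SARS-CoV-2 test, which for a control may precede delivery. But whether she is a neighbour of the case is settled only when both have delivered, so this does not remove the problem. That section also mentions an investigator manual that is not shown. It may specify an order, but the protocol text would still contradict itself.

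The consent wording may be a drafting slip, since the other sections consistently make controls PCR-negative. That is likely, and it still needs correcting.

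Stronger readings are tempting but unsupported:

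- A reader might infer a third control rule from the doctor's discretion in Patient referral sources. That sentence governs informing and consenting all patients and does not select controls.
- A reader might see a conflict with Substudy 3, Design. There, consecutive describes the hospitals' PCR screening, and a hospital can screen everyone without inviting everyone.
- A reader might conclude that every COVID odds ratio is biased. The 14-day neonatal and 6-week maternal outcomes are largely still open at prompt enrolment.

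**Conclusion.** The point holds with limits. The control rule is not deterministic, and on the protocol's own volume the cap would often leave a choice: about 69% of cases at an average site, on the Poisson assumption and the literal same-day wording. The choice would be among women whose delivery and early neonatal outcomes can be seen, and nothing written prevents its use. The Informed consent section contradicts the rule on mechanism and on infection status.

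Selection on outcome is permitted, not shown. The figure of 1.25 requires complicated controls to be taken 80% as often as uncomplicated ones and case enrolment to be unrelated to outcome; other assumptions give no bias or the opposite sign. This does not invalidate Substudy 3, but it should be corrected, because it is an avoidable route of bias into the substudy's only reported estimate. It cannot be left to an analysis plan, since controls are recruited at sites under the protocol.

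**What to change.** 1. In Substudy 3, Patients, state one deterministic rule. For example: the PCR-negative delivery immediately before the case and the next two after it, in delivery-register order, crossing midnight where needed, and moving to the next in order only for ineligibility or refusal. Remove the permissive fallbacks. A properly documented random draw would also prevent selection on outcome; what matters is that one rule is fixed and used throughout.
2. In Informed consent, describe the controls as PCR-negative women selected by that rule.
3. Keep a log of eligible, approached and enrolled women, with reasons for passing over anyone, and report the counts separately for cases and controls.
4. Recruitment began on 1 March 2020, and this version cites a source accessed on 3 August 2020, so at least five months of the recruitment period had passed. New wording cannot repair controls already enrolled. Check them against the delivery register and report a sensitivity analysis limited to those who conform to the rule.

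The cost is amendment wording, a short log kept by each site's existing data collector, and a one-off register check for past controls. It needs no extra patients or procedures.
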